#### Primary analysis

We will use a linear regression model to estimate differences in worst and average NRS scores between the two treatment groups, including baseline score and the minimisation variables as covariates. The P value from the associated χ^2^ test will be produced and used to determine statistical significance. A Bonferroni correction will be applied as there are two primary outcomes. Further analysis using a repeated measures (multilevel) model will also be performed incorporating all eight recorded scores.

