## Methods and analysis

### Study design

GaPP2 is a double-blind placebo-controlled randomised multicentre clinical trial (figure 1). We will screen women with CPP from up to 40 National Health Service hospitals within the UK. Women will return weekly NRS pain scores to the trials office for 4 weeks after initial consent. Those women meeting the inclusion criteria at the end of these 4 weeks will be randomised. We will randomise 300 women (150 to gabapentin, 150 to placebo). After randomisation and titration, participants will receive treatment with the maximum tolerated dose for 12 weeks. Participants and the healthcare team will be unblinded at the end of their treatment.

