### Intervention and randomisation

Randomisation to gabapentin or placebo will occur once written informed consent has been obtained, final eligibility established from the pain responses provided during the screening phase and baseline questionnaires completed. The Birmingham Clinical Trials Unit (BCTU) will provide third-party web-based randomisation with telephone backup. A minimisation procedure using a computer-based algorithm will be used to avoid chance imbalances in treatment allocation and the following potentially important variables:presence or absence of dysmenorrhoea (a pain score of ≥4/10 will be considered significant);psychological distress measured by the General Health Questionnaire (GHQ) (scored as 0–12 with a cut-off of 0–1 and 2–12 for minimisation);use of sex hormonal treatments (combined oral contraceptive, progestogens, levonorgestrel-releasing intrauterine system (Mirena));centre.

A ‘random element’ will be included in the minimisation algorithm, so that each patient has a probability (unspecified here) of being randomised to the opposite treatment that they would have otherwise received. Full details of the algorithm used will be stored in a confidential document at BCTU. Both participants and the research team will remain blind to allocation.

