### Sample size

We have based our sample size on being able to detect a minimally important difference (MID) in NRS scores with high levels of power. Studies have shown the MID in this population to be around 1 point on a 0–10 scale.^21^ Our pilot study showed worst and average pain scores to have SDs between 2.0 and 2.5. If the SD is at the lower end of these estimates, 86 patients in each group (172 in total) would be required to have 90% power (P=0.05) to detect a difference of 1 point. If the SD is at the higher end, we could detect the same difference with 80% power (P=0.05) with 100 patients in each group. We have assumed the latter SD (2.5) to be conservative. To account for any increase in the risk of type I error that may be associated with having coprimary outcome measures, we have applied a Bonferroni correction (alpha reduced to 0.025 from 0.05), which increases the sample size to 120 per group. Furthermore, to account for an expected average 20% lost to follow up, we will randomise 150 per group, 300 patients in total.

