### Proposed analyses

Data analysis will be by intention to treat. Every attempt will be made to gather data on all women randomised, irrespective of compliance with the treatment protocol. Appropriate baseline characteristics, split by treatment group, will be presented for each outcome. Point estimates, 95% CIs and P values from two-sided tests will be reported.

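### The primary P value is taken from a chi-square test after a linear regression, where a t test is exact under normal errors; the resulting type I error excess is small or moderate depending on choices the article does not state (minor)

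*Protocol article*

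**What the plan says.** Under Primary analysis, the Protocol article compares worst and average NRS scores between groups by linear regression, "including baseline score and the minimisation variables as covariates". It then fixes the decision rule: "The P value from the associated χ^2^ test will be produced and used to determine statistical significance". It does not say whether that is a likelihood-ratio, score or Wald test, or which variance estimate it uses.

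The minimisation variables are listed under Intervention and randomisation. They are dysmenorrhoea, GHQ in two categories, and finally "use of sex hormonal treatments (combined oral contraceptive, progestogens, levonorgestrel-releasing intrauterine system (Mirena));centre". Centre is therefore one of them. On the number of centres, Study design says "We will screen women with CPP from up to 40 National Health Service hospitals within the UK". The article does not say whether centre enters as fixed indicators or as a random effect.

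Tests are two-sided: "Point estimates, 95% CIs and P values from two-sided tests will be reported". The significance level for each outcome follows from Sample size: "we have applied a Bonferroni correction (alpha reduced to 0.025 from 0.05), which increases the sample size to 120 per group".

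**The concern.** In a linear regression the residual variance is estimated. The treatment coefficient divided by its standard error then follows a t distribution on the residual degrees of freedom, exactly so if the errors are normal with constant variance. A chi-square test is the large-sample approximation to this. It is too liberal, because it ignores the uncertainty in the variance estimate. In some forms it also divides the residual sum of squares by the number of women rather than by the residual degrees of freedom.

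The second effect grows with the number of fitted parameters. If centre is fitted as indicators, this model could have many of them for the number of women expected.

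The sentence concerns the P value that decides the trial. The plan raised its requirement from 100 to 120 women per group to protect the type I error across two outcomes, so the test should not give part of that protection back.

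**Working it through.** **Inputs from the Protocol article.** Two-sided alpha of 0.025 per outcome; difference of 1 point ("Studies have shown the MID in this population to be around 1 point on a 0–10 scale"); SD of 2.5 ("We have assumed the latter SD (2.5) to be conservative"); 80% power; 20% loss; 300 randomised; at most 40 centres.

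**Step 1: reproduce the plan's own figure.** Per group, n = 2 × (2.241 + 0.842)² × 2.5² / 1² = 118.8, so 119. The t-based calculation gives 120.1, and the plan states 120. Inflating for loss, 120 / 0.8 = 150 per group, or 300 in total. The sample size stands. It implies 2 × 120 = 240 women analysed.

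**Step 2: count parameters.** With C centres as fixed indicators, p = 1 (intercept) + 1 (treatment) + 1 (baseline) + 3 (binary minimisation variables) + (C − 1). For C = 40, p = 45 and the residual degrees of freedom are df = 240 − 45 = 195.

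**Step 3: express each chi-square rule as a rule on F.** Let c = 5.024, the 0.975 quantile of chi-square on 1 df, and let F be the squared t statistic on 1 and df degrees of freedom. Each test rejects when F exceeds the threshold shown (N = 240, C = 40):

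| Test | Threshold for F | Value | True size |
|---|---|---|---|
| Exact t/F | 0.975 quantile of F(1, 195) | 5.102 | 0.025 |
| Wald, residual variance RSS/df | c | 5.024 | 0.026 |
| Score | c·df/(N − c) = 5.024 × 195 / 234.976 | 4.169 | 0.043 |
| Likelihood ratio | df·(exp(c/N) − 1) = 195 × (exp(0.02093) − 1) | 4.125 | 0.044 |
| Wald, maximum-likelihood variance RSS/N | c·df/N = 5.024 × 195 / 240 | 4.082 | 0.045 |

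A simulation of the 40-centre model (20,000 runs, 240 women, normal errors) gave 0.044 for the likelihood-ratio test, 0.026 for the Wald test with residual variance and 0.024 for the F test.

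**Step 4: vary the number of centres and of women.** True size at nominal 0.025:

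| Fixed centres | Likelihood ratio, N = 240 | Likelihood ratio, N = 300 | Wald (RSS/df), N = 240 |
|---|---|---|---|
| no centre terms | 0.027 | 0.027 | 0.026 |
| 10 | 0.030 | 0.029 | 0.026 |
| 20 | 0.034 | 0.032 | 0.026 |
| 30 | 0.039 | 0.035 | 0.026 |
| 40 | 0.044 | 0.039 | 0.026 |

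The score and maximum-likelihood-variance Wald tests lie within about 0.001 of the likelihood-ratio column.

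**Step 5: family-wise error over two outcomes.** If the outcomes are independent:

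- planned: 1 − (1 − 0.025)² = 0.049;
- likelihood ratio, 40 centres, N = 240: 1 − (1 − 0.0436)² = 0.085;
- Wald with residual variance: 1 − (1 − 0.0261)² = 0.052.

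The article gives no correlation between average and worst pain. If the two test statistics are assumed to correlate at 0.5 or 0.8, the likelihood-ratio figure falls to about 0.080 or 0.069, and the Wald figure to about 0.048 or 0.042.

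**The case against.** The strongest reply is that the article names no particular chi-square test. A Wald chi-square with the ordinary residual variance is as literal a reading as any other. Under it the size is 0.026 whatever the number of centres, and the family-wise error is at or below about 5%.

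The larger figures also need centre to be fitted as fixed terms, which the article does not say. A random centre effect fits the text equally well. Under Secondary analysis, the bracketed list of minimisation variables names only the three clinical ones, although that list concerns predictors of response and does not show that centre is left out of the primary model. In addition, 40 is a ceiling on screening hospitals, not an expected number of contributing centres. These details commonly belong in a statistical analysis plan, which is not at hand.

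Most of this stands. A reader might infer that the trial's type I error is about 0.04 per outcome, or 8.5% overall, and that most of the Bonferroni protection is lost. The document does not support that. It would take a likelihood-ratio type of test, fixed centre terms and a centre count near the ceiling, all together; the 8.5% further needs independence between two pain scores from the same women over the same four weeks, which is implausible.

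What the reply does not remove is that the article states a chi-square rule and makes it decisive. That is a stated choice, not a detail left open. It is never better calibrated than the t test under the model's own assumptions.

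**Conclusion.** The point holds as a minor one. The chi-square P value is the wrong reference distribution for this model, and it errs in the liberal direction under every reading. The excess over 0.025 runs from about 0.001 (Wald with residual variance) to about 0.02 (likelihood-ratio type of test, 40 fixed centres, 240 women). Between these lie 0.030 at 10 centres and 0.034 at 20. The document does not settle where in this range the trial falls.

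The figures assume normal errors with constant variance, one parameter for each binary minimisation variable and, for the larger values, centre as fixed indicators. The family-wise figures of about 7% to 8% rest on assumed correlations. The sample size calculation is unaffected.

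**What to change.** Under Primary analysis, replace the sentence on the chi-square test with: *The P value from the two-sided t test of the treatment coefficient, on the residual degrees of freedom, will be judged against 0.025.*

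This removes the ambiguity over the type of chi-square test. With centre as fixed terms, it gives size 0.025 under normal errors whatever the number of centres.

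The cost is one sentence. P values become slightly larger: at 195 degrees of freedom the critical F is 5.102, against 5.024 for the Wald chi-square with residual variance. The shift is larger only where the chi-square would have been most liberal. Sample size and trial conduct do not change.

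### Holm in place of plain Bonferroni would raise power for each primary pain score, and for both together, at the same 5% family error and sample size

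*Protocol article*

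**What the plan says.** Average and worst pain on the 0–10 scale, both taken from weeks 13–16, are coprimary (Primary outcome section). For the analysis the article says: "A Bonferroni correction will be applied as there are two primary outcomes". The Sample size section gives the level and its consequence: "we have applied a Bonferroni correction (alpha reduced to 0.025 from 0.05), which increases the sample size to 120 per group". After 20% loss this becomes 150 per group.

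The planning inputs are a 1-point difference ("Studies have shown the MID in this population to be around 1 point on a 0–10 scale") and the upper end of the pilot SDs ("Our pilot study showed worst and average pain scores to have SDs between 2.0 and 2.5"; "We have assumed the latter SD (2.5) to be conservative"). On reporting, the Proposed analyses section says: "Point estimates, 95% CIs and P values from two-sided tests will be reported".

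The article mentions no step-down rule, gives no correlation between the two scores, and does not say in words whether one or both must be significant. Splitting alpha implies that either one suffices.

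**The concern.** Under the stated rule each P value is held to 0.025 even when the other null hypothesis has already been rejected. The Holm procedure compares the smaller P with 0.025 and, only if that is significant, the larger with 0.05. It rejects everything that Bonferroni rejects and sometimes more, and it controls the family error whatever the dependence between the tests.

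Take P = 0.01 for one score and P = 0.04 for the other. The present rule leaves the second not significant, whereas Holm rejects both at the same 5% family error.

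This matters here because, according to the Discussion, surveyed women were split on which score counts most (43.4% average, 56.6% worst). That is why both were made coprimary, so a conclusion on each score is of interest in its own right. At stake is some power for each score and for the pair. The validity of the trial is not in question.

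**Working it through.** **Inputs from the article.** Difference 1 point (applied here to both outcomes); SD 2.5 for planning, pilot range 2.0 to 2.5; two-sided tests; 0.025 per outcome; 120 analysable per group; 1:1 allocation. **Assumption:** correlation ρ between the two test statistics from 0 to 0.9, since none is given.

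**1. The plan's own figure.** n per group = 2·SD²·(z₁₋α/₂ + z₁₋β)²/δ² = 2 × 6.25 × (2.2414 + 0.8416)² = 118.8, so 119; the t-based value is 120.1. The article's 120 is reproduced, and 120/0.8 = 150. The other two stated sizes also reproduce to within one woman: 85 against 86 (SD 2.0, 90% power, 0.05) and 99 against 100 (SD 2.5, 80% power, 0.05).

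**2. Power for one outcome.** Mean of the test statistic: 1/(2.5 × √(2/120)) = 3.098. At 0.025: Φ(3.098 − 2.241) = 80.4%. At an unadjusted 0.05: Φ(3.098 − 1.960) = 87.3%. Bonferroni therefore costs about 6.8 points per outcome.

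**3. Holm against Bonferroni.** Let a = 2.241 and b = 1.960 be the critical values, and let S(x, y) be the probability that the first statistic exceeds x and the second exceeds y (bivariate normal, correlation ρ).
- Both significant: Bonferroni S(a, a); Holm 2·S(a, b) − S(a, a).
- A given outcome significant: Bonferroni 80.4%; Holm 80.4% + S(a, b) − S(a, a).
- At least one significant: 2 × 80.4% − S(a, a) under either rule, because Holm's first step is the Bonferroni test.

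Example at ρ = 0.8: S(a, a) = 0.734 and S(a, b) = 0.771. Both under Holm = 2 × 0.771 − 0.734 = 0.808. Per outcome = 0.804 + 0.771 − 0.734 = 0.841.

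SD 2.5, 120 per group, 1 point on both outcomes (Bonferroni → Holm):

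| ρ | Per outcome | Both | At least one (either rule) |
|---|---|---|---|
| 0 | 80.4% → 85.9% | 64.7% → 75.7% | 96.2% |
| 0.5 | 80.4% → 84.9% | 69.3% → 78.3% | 91.6% |
| 0.7 | 80.4% → 84.5% | 71.8% → 79.9% | 89.0% |
| 0.8 | 80.4% → 84.1% | 73.4% → 80.8% | 87.4% |
| 0.9 | 80.4% → 83.6% | 75.5% → 81.9% | 85.4% |

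**4. Lower SD.** At SD 2.0 the mean statistic is 3.873. Per outcome, power goes from 94.9% to 96.1–97.1%, and for both from 90.0–93.0% to 94.5–95.6%. The gains are about 1–2 and 3–4 points.

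**5. Unequal effects (SD 2.5).** With true differences of 1 and 0.5 points, power for the weaker outcome rises from 24% to 32–34%. If the second outcome has no effect at all, power for the first is 80.4% under Bonferroni and 80.4–80.5% under Holm.

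**6. Family error (2 million simulated draws per setting).** With both nulls true, the two rules have the same error: 5.0% at ρ = 0 and 4.0% at ρ = 0.8. With one null true and a 1-point effect on the other outcome, Holm's error is 3.7–4.5%. Neither rule exceeds 5% beyond rounding.

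**The case against.** The strongest reply is that nothing in the plan is wrong. Bonferroni is valid under any dependence, the analysis and the sizing use the same 0.025, and the target of 80% power per outcome is met. All of that stands: this is a gain in efficiency, and a reader who infers that the trial is mis-sized or its error uncontrolled would be mistaken.

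Two stronger readings are also tempting, and neither is supported.
- *That Bonferroni is wasteful here because the two scores are closely related, and that Holm recovers this loss.* The article gives no correlation, and Holm does not use one. Its gain for both outcomes falls from 11 points at ρ = 0 to about 6 at ρ = 0.9. The slack that correlation leaves in Bonferroni would be used only by a correlation-based critical value (about 0.031 per outcome at ρ = 0.8).
- *That Holm makes a positive trial more likely, or that showing both is improbable as planned.* If either outcome suffices, the chance of success is identical under both rules. Showing both is not a criterion that the article sets, and it already has 65–76% power at SD 2.5.

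It is also fair to say that SD 2.5 is the least favourable end of the pilot range, and that the planned adjustment for baseline should reduce the residual SD. If the baseline correlation were 0.5 (an assumption), the residual SD would be 2.5 × √0.75 = 2.17. Power for both would then go from 83–88% to 90–92%, and per outcome from 91% to 93–94%. The gain shrinks but does not vanish.

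Finally, Bonferroni pairs exactly with 97.5% intervals and Holm has no equally simple match. That is a real cost. However, the article announces 95% intervals, which already disagree with a 0.025 test whenever P lies between 0.025 and 0.05.

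**Conclusion.** The point holds as a cheap improvement. The stated rule is valid and matches the sample size, but Holm is at least as powerful in every case at the same family error and the same number of women. At the planning SD of 2.5, with 1 point on both outcomes, it adds about 3 to 5.5 points of power per outcome and 6 to 11 for both. At ρ = 0.8 it recovers 3.7 of the 6.8 points that Bonferroni costs each outcome. At SD 2.0 the benefit is small.

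These sizes rest on normal test statistics, 120 analysable women per group, equal true effects on both scores, and an assumed correlation between 0 and 0.9. The benefit arises only when both scores respond. The chance of at least one significant result stays the same.

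**What to change.** Before any unblinded data are seen, replace the Bonferroni sentence in the Primary analysis section with: *The smaller of the two primary P values is compared with 0.025; if it is significant, the larger is compared with 0.05 (Holm).*

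Keep the sample size calculation at 0.025, so the 120 and 150 per group stand. In the Proposed analyses section, specify 97.5% intervals for the two primary outcomes in place of 95%. Add a note that the second outcome's 97.5% interval may include zero although Holm rejects, when its P value lies between 0.025 and 0.05.

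The cost is one changed sentence on testing, one on intervals, and that note. No extra women, data or correlation estimate are needed. The price is a less tidy link between test and interval for the second outcome.

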#### Secondary analysis

Data from the other continuous measures (SF-12, BPI, PCS, SAQ, WPAIQ, BFI, PainDETECT and GHQ) will be analysed in a similar manner to the primary measure. Other outcome measures (use of permitted analgesic medication, satisfaction) will be analysed using standard methods (tests for trend, absolute/relative risks). Further analysis on pain scores will include an examination of the proportion of women that have a 30% and a 50% reduction in average and worst score from baseline as the outcome. A log-binomial regression model will be used here to generate adjusted relative risks. Subgroup analyses will be limited to the same variables that were used as minimisation variables. Tests for statistical heterogeneity (eg, by including treatment group by subgroup interaction parameter in the linear regression model) will be performed prior to any examination of effect estimate within subgroups. In addition, we will investigate up to nine clinical variables measured at baseline to determine whether they correlate with response to treatment. These will include the minimisation variables (the presence of dysmenorrhoea/psychological distress/current use of hormonal treatment) along with measures of intensity and of nature of pain (eg, PainDETECT), number of functional systems involved (as a measure of organ specific versus generalised pelvic pain syndrome) and PUF score.

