### Inclusion criteria

Women aged between 18 and 50 years.CPP (with or without dysmenorrhoea or dyspareunia) of >3-months duration.Pain located within the true pelvis or between and below anterior iliac crests.No obvious pelvic pathology at laparoscopy (laparoscopy must have taken place at least 2 weeks ago, but no more than 36 months prior to screening).Using or willing to use effective contraception if necessary to avoid pregnancy.Able to give informed consent.For both the worst and average prerandomisation NRS questions, at least three of the four weekly scores returned to the trials office. At least two of the worst pain scores should be ≥4/10. Potential participants who have been on a stable dose of an analgesic, other than gabapentin or pregabalin, for at least 4 weeks prior to screening will be eligible.

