### Dose regimen

After randomisation, participants will be allocated a trial treatment pack from the hospital pharmacy containing either gabapentin or placebo oral tablets, both of identical appearance. Participants will start on one capsule (300 mg) daily and will increase by one capsule (300 mg) increments every 3 days until they perceive that they are gaining adequate pain relief, or report side effects (eg, dizziness, somnolence, mood changes, appetite and poor concentration) that preclude them from further increases, up to a maximum dose of nine capsules (2700 mg), as shown in table 1. The titration phase will last a maximum of 4 weeks. If necessary they will be advised to titrate down to the last tolerated dose with minimal side effects. They will be asked to maintain their best tolerated dose until the end of week 16. Patients will be advised and given written instructions regarding their dosing regimen by a member of the research team. It will be recommended that the drug should be taken in three equally divided doses daily. The same protocol will be used for the placebo. When the participant stops treatment, the dose will be reduced according to a dose reduction chart and written instructions will be given. Patients will be allowed to use other medication (including analgesics, self-medication and alternative treatments, eg, acupuncture) throughout the study period.

**Table 1 T1:** Dose escalation schedule for GaPP2

Day in study	Total number of capsules/day (maximum)	Dosing	Maximum daily dose of gabapentin (mg)
1	1	One capsule night	300
2	1	One capsule night	300
3	1	One capsule night	300
4	2	One capsule two times a day	600
5	2	One capsule two times a day	600
6	2	One capsule two times a day	600
7	3	One capsule three times a day	900
8	3	One capsule three times a day	900
9	3	One capsule three times a day	900
10	4	One capsule two times+two capsules at night	1200
11	4	One capsule two times+two capsules at night	1200
12	4	One capsule two times+two capsules at night	1200
13	5	Two capsules two times+one capsule once	1500
14	5	Two capsules two times+one capsule once	1500
15	5	Two capsules two times+one capsule once	1500
16	6	Two capsules three times a day	1800
17	6	Two capsules three times a day	1800
18	6	Two capsules three times a day	1800
19	7	Two capsules two times+three capsules night	2100
20	7	Two capsules two times+three capsules night	2100
21	7	Two capsules two times+three capsules night	2100
22	8	Three capsules two times+two capsules once	2400

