#### Questionnaires

A questionnaire will be given to all participants before randomisation but after screening (baseline) and at 16 weeks postrandomisation (see table 2 for full schedule of assessments). This will include the following validated tools:

**Table 2 T2:** Schedule of outcome assessments for GaPP2

Phase	Run-in				Baseline, randomisation and treatment dispensed	Titration	Treatment					End of study and unblinding	Taper
Duration (weeks)	−4 to −1				0	1–4	5–12	13–16					17–19
Weekly worst and average NRS	**x**	**x**	**x**	**x**				**x**	**x**	**x**	**x**		
SF-12					**X**							**X**	
BPI					**X**							**X**	
PCS					**X**							**X**	
SAQ					**X**							**X**	
BFI					**X**							**X**	
GHQ					**X**							**X**	
WPAIQ					**X**							**X**	
PainDETECT					**X**							**X**	
PUF					**X**								
Adverse events						**X**	**X**	**X**				**X**	**X**
Permitted/concomitant medication	**X**					**X**	**X**	**X**					**X**
Adherence or discontinuation						**X**	**X**	**X**					**X**

BFI, Brief Fatigue Inventory; BPI, Brief Pain Inventory; GHQ, General Health Questionnaire; NRS, Numerical Rating Scale; PCS, Pain Catastrophising Scale; PUF, Pelvic Pain and Urinary/Frequency Patient Symptom Scale; SAQ, Sexual Activity Questionnaire; SF-12, 12-Item Short-Form Health Survey; WPAIQ, Work and Productivity Activity Impairment Questionnaire.

12-Item Short-Form Health Survey (SF-12): a QoL measure.^13^Brief Pain Inventory (BPI)^14^: a tool to measure pain intensity and interference of pain in a patient’s life.Brief Fatigue Inventory (BFI).^15^GHQ^16^: to identify psychological distress.Work and Productivity Activity Impairment Questionnaire (WPAIQ).^17^Pain Catastrophising Scale (PCS).^18^Sexual Activity Questionnaire (SAQ).^19^PainDETECT: to identify a neuropathic component to pain.^20^Pelvic Pain and Urinary/Frequency Patient Symptom Scale (PUF) (at baseline only).

The questionnaire at baseline will include questions to capture the baseline demographic and clinical characteristics of the participants.

All questionnaires will be anonymised and completed in private.

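### Analgesic use is to be compared by trend tests and risks with no covariates named, although run-in use is recorded: unbiased, but precision is given up

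*Protocol article*

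**What the plan says.** The protocol article uses three kinds of analysis for its treatment comparisons.

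- **Coprimary pain scores (Primary analysis).** Linear regression "including baseline score and the minimisation variables as covariates".
- **Continuous questionnaires (Secondary analysis).** These "will be analysed in a similar manner to the primary measure", so they inherit the same adjustment. For 30% and 50% pain reduction the section adds: "A log-binomial regression model will be used here to generate adjusted relative risks".
- **Analgesic use and satisfaction (Secondary analysis).** "Other outcome measures (use of permitted analgesic medication, satisfaction) will be analysed using standard methods (tests for trend, absolute/relative risks". No covariate is named.

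Three other places bear on analgesic use. Under Inclusion criteria, women already taking analgesics may enter: "Potential participants who have been on a stable dose of an analgesic, other than gabapentin or pregabalin". Under Dose regimen, other treatment is unrestricted: "Patients will be allowed to use other medication (including analgesics, self-medication and alternative treatments, eg, acupuncture) throughout the study period". In Table 2 (Questionnaires) the row "Permitted/concomitant medication" is marked in the run-in, titration, treatment and taper. Participant-reported analgesic use is itself listed under Secondary outcomes.

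**The concern.** Some women enter on a stable analgesic and others on none, so use before treatment differs between women and is likely to predict use afterwards. The trial records it beforehand, yet the comparison planned for this outcome names neither run-in use nor the minimisation variables. The same section adjusts the questionnaires and describes the pain-response relative risks as adjusted, so the missing word here looks like a choice.

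The stake is interpretation. With analgesics freely allowed, similar pain scores mean one thing if analgesic use is also similar and another if one arm needs less. Analgesic use is the outcome that separates these readings. The Sample size section sizes the trial on pain scores alone, so precision on analgesic use is whatever the analysis can extract. Where the minimisation factors are prognostic, leaving them out after minimised allocation also tends to make standard errors too wide and tests conservative.

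**Working it through.** **1. What is held.** Run-in medication use is marked in Table 2. Dysmenorrhoea, GHQ category, sex hormone use and centre are known at allocation (Intervention and randomisation). The adjustment needs no new data item, subject to the point about measurement under the objection.

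**2. Number per arm.** The article gives no figure for analgesic use, so the only figure to reproduce is the number per arm. For a 1-point difference, SD 2.5, two-sided alpha 0.025 and 80% power:

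n = 2 × (2.241 + 0.842)² × 2.5² / 1² ≈ 119 per arm (121 with the t distribution).

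The article states 120, and 120 / 0.8 = 150. Its figures reproduce, and this point does not touch them. I use 120 per arm below.

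**3. Assumptions, none of them from the article.** Analgesic use is treated as yes or no. Run-in use is 60%, the true fall in use on gabapentin is 15 percentage points, and the test is two-sided at 0.05. How well run-in use predicts later use is varied.

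**4. Formulas.** With p the proportion using analgesics at follow-up:

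- Unadjusted variance = [p_P(1 − p_P) + p_G(1 − p_G)] / 120.
- Adjusted variance ≈ the same expression, with each p(1 − p) replaced by its average within run-in users (weight 0.6) and non-users (weight 0.4).

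Moderate case: placebo use is 80% in run-in users and 30% in non-users, so 65% and 15% on gabapentin, and 60% v 45% overall.

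- Unadjusted: (0.6 × 0.4 + 0.45 × 0.55) / 120 = 0.4875 / 120, so SE = 0.0637.
- Placebo, within strata: 0.6 × 0.8 × 0.2 + 0.4 × 0.3 × 0.7 = 0.180.
- Gabapentin, within strata: 0.6 × 0.65 × 0.35 + 0.4 × 0.15 × 0.85 = 0.1875.
- Adjusted: 0.3675 / 120, so SE = 0.0553.

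**5. Simulation.** 3000 runs per case, linear model for the risk difference with robust SE, with and without run-in use:

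| Run-in use predicts | Placebo use at follow-up, run-in users / non-users | SE unadjusted | SE adjusted | Ratio | Power |
|---|---|---|---|---|---|
| Weakly | 70% / 50% | 0.0636 | 0.0624 | 0.981 | 0.63 to 0.66 |
| Moderately | 80% / 30% | 0.0637 | 0.0555 | 0.870 | 0.63 to 0.78 |
| Strongly | 90% / 20% | 0.0636 | 0.0456 | 0.718 | 0.63 to 0.92 |

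The equivalent increase in sample size is 1 / ratio² − 1: about 4% (1 / 0.981²), 32% (1 / 0.870²) and 94% (1 / 0.718²).

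**6. Cross-check by formula.** For 60% v 45% with 120 per arm, the two-proportion formula gives unadjusted power of 0.645, close to the simulated 0.63. If covariates explain a share R² of the outcome variance, the SE is multiplied by √(1 − R²) and the effective number is 120 / (1 − R²):

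| R² | SE factor | Power |
|---|---|---|
| 0.05 | 0.975 | 0.667 |
| 0.10 | 0.949 | 0.691 |
| 0.20 | 0.894 | 0.742 |
| 0.30 | 0.837 | 0.797 |
| 0.50 | 0.707 | 0.911 |

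Adjustment helps in every case. How much it helps depends on a correlation that the article does not give. No gain was calculated for the minimisation variables or for satisfaction.

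**The case against.** The strongest reply is that a condensed article is being read too closely. It never says these comparisons are unadjusted. A relative risk is an effect measure and can be adjusted, as the pain-response analysis shows, and a covariate list for a lesser secondary outcome commonly sits in the analysis plan. This stands in part: the unadjusted reading is an inference. But the sentence does fix a method. It sets these two outcomes apart from the adjusted questionnaires, and the word adjusted appears for one set of relative risks and not for the other. If adjustment was intended, the sentence needs the same correction.

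Other objections stand and limit the point:

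- A reader might infer that the comparison is biased or invalid. It is not. Randomisation protects it, and omitting minimisation factors errs towards conservative tests.
- A reader might infer that satisfaction suffers equally. It rates the treatment and has no run-in counterpart, so only the minimisation variables could help, by an unknown and possibly small amount.
- Table 2 does not say whether run-in medication is recorded as yes or no, drug, dose or frequency, and the items listed under Treatment diaries do not name analgesics. Whether use is measured alike before and after treatment cannot be established from the article.
- Trend tests suggest that at least one of these outcomes is ordered, which the yes-or-no illustration does not cover.
- Analgesic use is one of eight secondary outcome items and appears in neither stated objective.

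**Conclusion.** The point holds as a loss of precision on one secondary outcome. As written, the article plans to compare analgesic use without the covariates it uses elsewhere, although it records run-in use and holds the minimisation variables. That comparison would be valid but less precise than it need be.

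Under the stated assumptions the SE falls by about 2% to 28%, and power rises from about 0.63 to between 0.66 and 0.92. This range rests on assumed rates, an assumed 15-point difference and a yes-or-no measure taken alike at both times. The article supports no single figure within it, so a large loss of power should not be claimed. The coprimary analysis and the sample size are unaffected. This is an essentially free improvement, not the repair of an error.

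**What to change.** Replace the sentence before any unblinded analysis, to state three things:

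1. Analgesic use will be compared by a regression including run-in analgesic use and the minimisation variables, with adjusted absolute and relative risks reported. The log-binomial approach already planned for pain response would serve for the relative risk, and the absolute difference can be obtained from standardised model predictions. If use is graded in ordered categories, an ordinal model with the same covariates replaces the trend test.
2. Analgesic use is defined in the same way in the run-in and at follow-up.
3. Satisfaction will be adjusted for the minimisation variables only, for consistency.

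The choice among acceptable models is a matter of preference. Centre needs some thought: 300 women over up to 40 hospitals is 300 / 40 = 7.5 per centre if all take part, so a model for a binary or ordered outcome may be unstable with many centre terms. Its handling should be settled in advance.

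The cost is wording only. No further data, women or visits are needed, provided the run-in medication record can be put into the same form as the follow-up record.
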